#### Data analyses

The ORIC scores will be analysed descriptively. AIM and FIM will be summed with means calculated for each measure. Higher scores will indicate better acceptability and feasibility.^62^ Fidelity scores will be analysed using a linear mixed-effects model to compare the effectiveness of the two implementation strategies on fidelity. Subgroup analysis will also be conducted to provide additional insights into the effectiveness of the implementation strategy on fidelity in specific contexts. All quantitative data will be analysed using STATA V.18 (StataCorp LLC, College Station, Texas, USA). The qualitative interviews on facilitators, barriers and contextual factors to adopt oral AZM will be analysed using deductive methods based on CFIR domains and inductive methods using Braun and Clarke’s thematic analysis approach.^63^ Other qualitative interviews to assess fidelity, feasibility, acceptability and sustainability will also be analysed thematically using Braun and Clarke’s approach.^63^ Dedoose V.9.0.17 (SocioCultural Research Consultants, LLC, Los Angeles, California, USA) will support our qualitative analysis.

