**Methods and analysis:**

This is a multicentre hybrid type 2 trial conducted in six Nigerian states: Ebonyi, Edo, Gombe, Kano, Kwara and Lagos. The study aims to simultaneously test the clinical and cost-effectiveness of AZM (clinical trial) and the impact of implementation strategies (implementation research) in Nigeria’s unique healthcare context. The clinical trial is a two-arm, cluster-randomised controlled trial conducted across 48 health facilities, randomly assigned (1:1) to either intrapartum administration of oral AZM (intervention group) or usual care—the current routine practice (control group). A total of 5040 study participants (2520 in each group) will be enrolled in the clinical trial. The implementation trial is a two-arm cluster non-randomised controlled trial conducted in 12 health facilities (1:1) allocated to either a bottom-up approach using the Plan-Do-Study-Act cycle or a usual top-down approach with a one-time training workshop and distribution of clinical guidelines, with both arms administering oral AZM during vaginal birth while assessing fidelity (primary outcome).

For the clinical trial, data will be analysed using intention-to-treat statistical methods. The cost-effectiveness outcome will be analysed using the Incremental Cost-Effectiveness Ratio. Implementation outcomes will be analysed using descriptive statistics and a thematic approach.

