### Implementation trial

#### Study design

The implementation trial is conducted as a two-arm, cluster non-randomised controlled trial with a parallel process evaluation. For this, 12 health facilities (clusters) were allocated to the intervention (PDSA cycle) and comparison (usual strategy) sites (figure 1), based on logistics and interest in facility-level outcomes (SHP’s adherence to oral AZM administration according to protocol).^50^ The six intervention sites will use the PDSA cycles to co-design, refine and adapt context-specific implementation strategies to enhance SHP’s adherence to oral AZM as part of a sepsis prevention protocol for maternal sepsis during vaginal birth. The six comparison sites will implement oral AZM during vaginal birth using the usual strategy for adopting new treatments—a one-off training workshop and guideline distribution. Then, fidelity in healthcare facilities that used PDSA cycles to generate implementation strategies will be compared with those that used the usual strategy to understand which strategies work best and how they are effective in various settings.

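### Fidelity in 6 versus 6 non-randomised facilities: the modelled outcome is not clearly the one defined, no baseline adjustment is stated, and inference for 12 clusters is left open

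*Protocol article*

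**What the plan says.** All references are to the protocol article.

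- **Design.** The implementation trial (Study design) is a "two-arm, cluster non-randomised controlled trial with a parallel process evaluation". Its "12 health facilities (clusters) were allocated to the intervention (PDSA cycle) and comparison (usual strategy) sites", six per arm, "based on logistics and interest in facility-level outcomes". Study sites adds that the facilities were chosen purposively from a pool that had undergone a readiness assessment.
- **Outcome.** Outcome measures and Table 4 define fidelity, the primary outcome, as the proportion of vaginal births in which azithromycin was given per protocol. Adherence means meeting at least 70% of the essential components. Table 4 schedules it at midline and endline.
- **Analysis.** Data analyses states: "Fidelity scores will be analysed using a linear mixed-effects model to compare the effectiveness of the two implementation strategies on fidelity". It names no covariates, estimation method or degrees-of-freedom method.
- **Readiness.** ORIC is measured before the trial at all 12 facilities (Data collection methods). Data analyses gives its use: "The ORIC scores will be analysed descriptively".
- **Abstract.** Under Methods and analysis: "Implementation outcomes will be analysed using descriptive statistics and a thematic approach".

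**The concern.** Three things are unsettled in the analysis of the implementation primary outcome.

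1. **What is analysed.** The definition is a proportion of births passing a threshold. The model is of scores. A mean component score and a proportion above 70% are different quantities and can differ in size and even in direction. The abstract adds a third version, in which there is no model at all.
2. **Confounding.** The arms were not formed by chance, so the facilities may differ in ways that affect fidelity. For the randomised clinical trial, Statistical methods and analysis does name adjustment, for stratification variables and baseline imbalance. For the comparison more exposed to confounding, none is named, and ORIC is assigned to description.
3. **Precision.** The contrast between arms rests on 12 facilities, however many births are observed. Large-sample inference from a mixed model would then be too optimistic.

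At stake is the third objective, the effect of tailored strategies on fidelity: its interval could be too short, and existing differences between facilities could be credited to PDSA.

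**Working it through.** The implementation trial gives no sample size, power or significance level, so there is no planned figure to reproduce.

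**Inputs from the article**
- Clusters: 6 + 6 = 12 (Implementation trial, Study design). Degrees of freedom for the arm contrast: 12 − 2 = 10.
- Births per facility: the site criterion of 20 vaginal births a month × 9 months of monitoring = 180.

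**Assumptions, not in the article**
- Two-sided 5% level (stated for the clinical trial only).
- Intraclass correlation 0.01 to 0.20; true fidelity 50%, 70% or 85%.
- Also tried: 450 births per facility, and unequal sizes from 180 to 1,500.
- No true effect and no confounding.

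**Type I error by formula**

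With equal facility sizes, the statistic is T = (difference of arm means) / √(s² × 2/6), where s² is the variance between facility means. With s² estimated on 10 df, T follows t with 10 df.

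- REML, normal reference: 2 × P(t₁₀ > 1.96) = 0.078.
- ML, normal reference: the variance is divided by 12 rather than 10, so the effective cut-off is 1.96 × √(10/12) = 1.789, and 2 × P(t₁₀ > 1.789) = 0.104.
- REML, t with 10 df: 0.050.

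**Interval width**

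The 97.5% point of t₁₀ is 2.228. Under REML, the normal-based interval is 1 − 1.96/2.228 = 12% too narrow. Equivalently, the right interval is 2.228/1.96 = 1.137 times as wide, or 14% wider.

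**Simulation with yes/no births**

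Beta-binomial data were analysed with a random-intercept linear model: 40,000 runs per balanced scenario, 3,000 per unequal-size scenario.

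| Reference | Type I error across scenarios |
|---|---|
| REML, normal | 7.1–8.1% |
| ML, normal | 9.8–10.9% |
| REML, t with 10 df | 4.2–5.2% |
| t-test on 12 facility proportions (unequal sizes) | 4.9–5.0% |

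The third row shows that a linear model on yes/no data keeps its level, or falls slightly below it, once the degrees of freedom are right. The inflation comes from having 12 clusters.

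**Effect of adding ORIC**

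One facility-level covariate leaves 12 − 3 = 9 df. With a normal reference the error is 2 × P(t₉ > 1.96) = 8.2% (REML), or 2 × P(t₉ > 1.96 × √(9/12)) = 12.4% (ML). With t on 9 df it is 5%. Adjustment therefore does not repair the inference, and a small-sample reference does not remove confounding. Both are needed.

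The size of any confounding cannot be computed from the article.

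**The case against.** The strongest defence is that the article fixes very little here, and a fuller plan may supply what is missing. Four stronger readings are tempting, and the text does not support them.

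- **That the plan has an 8–10% false-positive rate.** It names a linear mixed-effects model but no normal reference, no estimation method and no degrees-of-freedom method. The same model with t on 10 df holds about 5%. The inflation is conditional.
- **That the model is unadjusted and ORIC is ignored.** No covariates are listed, but nothing says there will be none. ORIC is reported, it serves in Table 4 as a baseline measure of adoption, and readiness was assessed when sites were selected. What can be said is that no adjustment is stated and that the only analysis role given to ORIC is descriptive.
- **That keener facilities went to PDSA.** The allocation wording refers to interest in facility-level outcomes. This reads more naturally as the study's interest in such an outcome than as facilities volunteering. Allocation is still non-random, but no direction of bias follows.
- **That a linear model is wrong for a yes/no outcome.** A linear mixed model of facility proportions at midline and endline would be reasonable and may be what is meant. The simulations show no inflation from the yes/no outcome itself.

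It is also fair that the trial is openly labelled non-randomised, and that its Sample size section says the work is not meant for generalisation. However, the strengths and limitations list and the Introduction expect the results to inform adoption elsewhere in Africa and beyond.

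What remains does not depend on silence: the outcome definition and the modelled quantity do not clearly match, the abstract and Data analyses disagree, and a baseline score held for every facility is given only a descriptive role in a comparison open to confounding.

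**Conclusion.** The point holds in this limited form and should be dealt with before the arms are compared. The sections do not agree on whether fidelity is a score or a threshold proportion, or on whether it is modelled or only described. No adjustment is stated for a non-randomised 6 versus 6 comparison.

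The numerical consequence is moderate and conditional. Only if a normal reference is used does the type I error rise to the 7.8% or 10.4% shown above. These figures assume a two-sided 5% level and no confounding, and they change little over the assumed ranges of intraclass correlation, fidelity and facility size. Bias from non-random allocation would come on top and cannot be sized.

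A reader might infer that no sound conclusion on the third objective is possible. That goes too far: such a conclusion is not secured by the text as it stands, and changes of wording can go most of the way to securing it.

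**What to change.** 1. **Define the outcome once.** State whether fidelity is the proportion of births meeting the 70% rule or a component score, and at what level it is analysed. Use that in Outcome measures, Table 4 and Data analyses.
2. **State small-sample inference.** Analyse the facility-level fidelity proportions, or use a mixed model with small-sample degrees of freedom. Refer the arm contrast to t on at most 10 df.
3. **Adjust for baseline ORIC.** This leaves 9 df. Show facility level and birth volume by arm.
4. **Label the result.** Report the adjusted difference as a non-randomised estimate that may carry residual confounding.
5. **Align the abstract** with the comparative analysis in Data analyses.

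No new data are needed, because ORIC is already collected at all 12 facilities. The cost is one degree of freedom and a wider interval: relative to a normal-based REML interval, about 14% wider with t on 10 df, and slightly more with 9.

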#### Integration

Quantitative and qualitative data will be integrated during data collection and analysis and merged during the interpretation phase to provide a comprehensive understanding of the effect of implementation strategies on fidelity and factors influencing implementation outcomes.

### Ancillary and post-trial care

All participants are covered by clinical trial insurance in case of serious adverse drug events arising from the use of trial drugs. There are no specific plans for post-trial care.

### Patient and public involvement

Before the trial commenced, IDIs were conducted at two health facilities, involving purposively sampled 10 healthcare personnel (five nurses, four doctors and one laboratory technician) and 20 pregnant women, to understand their views, expectations, concerns and suggestions regarding the AZIN-V trial. The trial protocol was adapted based on their feedback.

### Research governance

The TMG is responsible for ensuring high-quality delivery of the trial in accordance with the protocol and addressing problems promptly. The TMG includes the chief investigator, coinvestigators, trial manager and data manager. The TMG reports to the independent TSC and the independent DSMB. The TSC will provide independent oversight and advice to the trial, while the DSMB is responsible for monitoring the trial data, including safety and data integrity. The independent DSMB will monitor all SAEs and review SAE events by masked treatment group at each meeting and report to the TSC. The DSMB will consist of a global health physician ([name], Harvard T.H. Chan School of Public Health, USA), a paediatrician ([name], University of Calabar, Nigeria) and a medical biostatistician ([name], London School of Hygiene and Tropical Medicine, UK). Auditing of research records will be conducted by the monitoring committees as outlined above, while financial auditing will be conducted by the Research Management Office and the Audit Department of the University of Lagos.

### Ethics and dissemination

#### Ethical considerations

Ethical approval has been obtained from the National Health Research Ethics Committee (NHREC), Nigeria (NHREC/01/01/2007-30/09/2024), the ethics committees of the participating health institutions (Lagos University Teaching Hospital Research Ethics Committee: ADM/DSCST/HREC/APP/6325; University of Ilorin Teaching Hospital Health Research Ethics Committee: ERC/PAN/2025/03/0581; University of Benin Teaching Hospital Health Research Ethics Committee: ADM/E22/A/VOL. VII/483117141; Aminu Kano Teaching Hospital Research Ethics Committee: AKTH/MAC/SUB/12 A/P-3/VI/2509; Irrua Specialist Teaching Hospital Research Ethics Committee: ISTH/HREC/20241507/605) and the states’ health ethics boards. Regulatory approval was obtained from the National Agency for Food and Drug Administration and Control. The trial is duly registered in the International Standard Randomised Controlled Trial Number (ISRCTN16415327) registry.

Written consent for participation, including consent for community tracking and assessing health records, is obtained from all eligible women (online supplemental material).^64 65^ Women aged 15–18 years are considered capable of providing consent, as they are considered emancipated for the purposes of this study, according to the guidelines of the NHREC and the 2016 WHO International Ethical Guidelines for Health-Related Research Involving Humans. Additional consent for de-identified data and samples is obtained for future studies or data sharing with secondary researchers.

This research protocol acknowledges the essential clinical responsibilities of health facility staff involved in the study, particularly in data collection and administration of the investigational drug to enrolled participants. To minimise disruption to their routine clinical duties, the following measures were implemented: (1) two trained research nurses are assigned per facility to assist with research tasks (data collection and participant tracking/follow-up) to ease the workload of regular clinical staff; (2) research activities are scheduled in coordination with facility management to avoid peak clinical hours and ensure uninterrupted patient care; (3) facility clinical staff’s participation in research is limited, clearly communicated and will not extend beyond their agreed working hours; (4) continuous monitoring is carried out to promptly identify and address any negative impact of research activities on clinical workflow and patient care and (5) participation of clinical staff in research tasks is voluntary, with the option to withdraw at any time without negative consequences.

Confidentiality of data obtained from participants will be maintained throughout the trial. All data collected at the study sites on REDCap are stored centrally in a password-protected electronic database by the senior data manager, who is the only person with access to the blinded data of all participants, collated centrally. Any approved modification to the protocol will be communicated to the investigators, and retraining of study staff on the amended protocol will be done as necessary.

#### Dissemination

The findings of this research will be shared through presentations at various scientific conferences in the fields of obstetrics, infectious diseases and public health, with publication in peer-reviewed journals and engagement with healthcare providers and relevant policymakers globally. Community engagement events and press releases will be used to communicate the results to the public and study participants.

### Trial status

The current protocol is V.3.0, 02 December 2025. The first participant was enrolled on 17 March 2025, and recruitment is projected to end by March 2026. The trial registration dataset is available on: https://www.isrctn.com/ISRCTN16415327.
